#### Cost-effectiveness

In order to derive the total utility experienced over the course of the investigation, the number of QALYs per patient will be calculated as the area under the utility curve.

Uncertainty around the estimates of costs and health outcomes will be addressed by bootstrapping the data with bias correction and acceleration (BCa) [47,48]. The 95% confidence interval around the difference in mean costs and health outcomes will be determined by taking the 2.5^th ^percentile and the 97.5^th ^percentile of these bootstrap replications. The bootstrap replicates will be plotted in cost-effectiveness planes (CE-planes). A CE-plane is an *x-y*-diagram with the *x*-axis representing the difference in health outcome between the treatment and usual care group and the *y*-axis representing the difference in costs. By plotting all bootstrap replicates in this diagram the uncertainty around the point estimates of the ICERs will be displayed [47]. The information from the CE-planes will be summarised into cost-effectiveness acceptability curves, which represent the likelihood that early assisted discharge is the most cost-effective option at different values of the maximum acceptable willingness to pay (WTP) for a health outcome [48].

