### Follow up visits

For both treatment groups two follow up visits at the outpatient clinic are scheduled at one month and three months after randomisation. During these visits patients are seen by their own pulmonologist and a respiratory nurse. The visits to the pulmonologist are as in usual care, the visits to the respiratory nurse have a twofold purpose. Firstly, these visits focus on the different aspects of disease management. It is at the discretion of the respiratory nurse which aspects need to be addressed in each specific patient. Secondly, these visits are used to collect, dispense and administer the questionnaires and cost diaries. Additional visits can be planned at the discretion of the pulmonologist (e.g. for additional testing) but do not fall under the study protocol. At the three month follow up visit lung function testing and a six minute walking distance test are performed as well.

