### Data collection

Data are collected on five time points: on the first day of admission (T0), on the third day of admission (randomisation, T1), at the end of the supervised treatment (day 7, T2) and one month (T3) and three months after randomisation (T4).

We use self-administered questionnaires and cost diaries to obtain data. The questionnaires are administered when supervision is available. Cost diaries are supplied at two time points (T2 and T3) for the up coming period, collected at the end of each follow up period and if necessary completed under supervision.

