### Effect evaluation

Table 2 provides an overview of the measures of the effect evaluation and the economic evaluation, and at which time point the measurements are performed.

**Table 2 T2:** Overview of measurements per time point

Measurement	T0	T1	T2	T3	T4
					

Demographic characteristics	x				

Smoking	x				

Body Mass Index	x				

Living situation	x				

Comorbidity	x				

Coping style (UCL)		x			

Medical treatment prior to admission	x				

Exacerbation severity	x				

Indication for admission	x				

Clinical COPD Questionnaire (CCQ)	x	x	x		x

EuroQol 5D (EQ-5D)		x	x		x

Satisfaction					

patient satisfaction			x		x

primary caregiver satisfaction			x		x

Caregiver Strain Index			x		x

Treatment Failures			x		

Readmissions					x

Mortality					x

Cost diary			x (IG)	x	x

Discrete Choice Experiment				x	

Lung function testing					x

6 Minute Walking Distance					x

T0 = baseline; T1 = randomisation; T2 = end of supervised treatment; T3 = follow up 1; T4 = follow up 2; IG = intervention group only

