#### Secondary outcome measurements

Main secondary outcome measurement of the study is the cost-effectiveness. This will be discussed in the economic evaluation section. The following other secondary measurements will be performed. These correspond with the secondary research questions from the last paragraph of the introduction:

1. Long-term effectiveness, measured with the CCQ change over the time points from day 1 to the end of the follow-up period (T4).

2. Number of treatment failures.

3. Number of readmissions to hospital and time to readmission during the three months follow-up period.

4. Mortality and time to death during the three months follow-up.

5. Generic health related quality of life, measured with the EuroQol (EQ-5D) 5D [41]. The EQ-5D will also be used to calculate quality adjusted life year (QALYs), discussed in the economic evaluation section.

6. Effects on primary informal caregiver burden measured by the Caregiver Strain Index [42].

7. Patient and primary informal caregiver satisfaction with the program. We use a translated version of the satisfaction questionnaire used by Ojoo et al. [24] and extended it with additional questions.

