Health outcomes will be related to cost outcomes. If one of the treatment options is more effective but also more costly, results will be presented as an incremental cost-effectiveness analysis: the additional cost per additional unit of health gain, which is calculated as the difference in mean costs between early discharge and usual inpatient hospital care divided by the in mean health effects.

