### Data analysis

Data analysis will be performed according to the intention to treat principle. Data from patients who die, quit participation or are otherwise lost to follow up will be included in the analysis up until the point of drop out. Missing observations will be imputed or weighted appropriately.

All primary and secondary outcome measurements will be analysed using analysis of covariance. In order to control for dependency between the repeated measurements within one patient, and for the dependency between patients from the same hospital, multilevel analyses will be performed as well. We set the significance level at α = 0.05.

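### QALYs use EQ-5D at randomisation, day 7 and month 3 only, so one straight line covers about 96% of follow-up time; no adjustment for T1 utility is stated for the QALY difference

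*Protocol article*

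**What the plan says.** All references are to the Protocol article.

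- **Source of the QALYs.** Secondary outcome measurements: "The EQ-5D will also be used to calculate quality adjusted life year (QALYs), discussed in the economic evaluation section". The Cost-effectiveness section then says that "the number of QALYs per patient will be calculated as the area under the utility curve".
- **Schedule.** Data collection places two readings early, "on the third day of admission (randomisation, T1), at the end of the supervised treatment (day 7, T2"), and two at follow-up, "one month (T3) and three months after randomisation (T4"). In Table 2 the EQ-5D row is marked at T1, T2 and T4; T0 and T3 are blank.
- **One-month visit.** Follow up visits says of the respiratory nurse visits at one and three months that "these visits are used to collect, dispense and administer the questionnaires and cost diaries". Table 2 has the cost diary and the discrete choice experiment at T3.
- **Costs.** Economic evaluation counts costs over the three months after randomisation, from diaries and hospital records.
- **Effect measure.** Economic evaluation defines the incremental ratio as "the difference in mean costs between early discharge and usual inpatient hospital care divided by the in mean health effects" (a word appears to be missing before the last phrase). Cost-effectiveness bootstraps the differences in means. Neither mentions covariates.
- **General rule.** Data analysis assigns analysis of covariance to every primary and secondary outcome. Secondary outcome measurements calls cost-effectiveness the main secondary outcome. Covariates are listed only for the primary CCQ analysis.
- **Deaths.** Data analysis: "Data from patients who die, quit participation or are otherwise lost to follow up will be included in the analysis up until the point" of drop-out. Missing observations are then to be imputed or weighted, with no separate statement for death.

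**The concern.** The numerator and the denominator of the cost-effectiveness ratio are observed with very different resolution. Costs accumulate throughout the three months. Utility between day 7 and month 3 is known only at the two ends, so any difference between the arms that departs from the straight line in between is invisible. Readmission during follow-up is a named secondary outcome, and it is the kind of event that adds cost and may lower utility in that interval.

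Separately, T1 utility is collected but has no stated role in estimating the QALY difference. A chance imbalance at T1 tends to persist, and then passes into the QALY difference as if it were a treatment effect. The general promise of analysis of covariance and the plain difference in means in the economic sections do not say the same thing about this.

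Cost-effectiveness is part of the primary research question, so both points deserve attention.

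**Working it through.** The plan gives no figure for the QALY calculation, so there is nothing of its own to reproduce here.

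**Inputs.** From the plan: T1 = day 3 and T2 = day 7 of admission, hence 4 days apart; T3 and T4 at one and three months after randomisation; revised sample size 165. Assumed: one month = 30 days, three months = 91 days, all utility values, utility SD and slopes.

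**1. Share of follow-up on one line.** (91 − 4)/91 = 87/91 = 95.6%. If three months is 84 to 92 days, the share is 95.2% to 95.7%. If T1 to T2 is also allowed to be 3 to 5 days, it is 94.1% to 96.7%. This is a share of time. The share of area depends on the utilities and was 94.7% to 97.3% over assumed profiles between 0.3 and 0.8.

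**2. Trapezoid weights.**
- T1: 2/91 = 2.2%
- T2: (2 + 43.5)/91 = 50.0%
- T4: 43.5/91 = 47.8%

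The QALY is close to the average of the day-7 and month-3 readings.

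**3. With EQ-5D at T3.** The segments become 4/91 = 4%, 26/91 = 29% and 61/91 = 67%. The longest straight segment falls from about 96% to about 67%.

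**4. What an off-line arm difference at T3 would be worth.** A mean difference d away from the T2–T4 line adds a triangle of area d × 87/2 days.
- d = 0.02: 0.02 × 43.5/365 = 0.0024 QALY
- d = 0.05: 0.0060 QALY
- d = 0.10: 0.0119 QALY

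The document gives no basis for choosing among these values.

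**5. Chance imbalance at T1.** With SD 0.25 and 165 patients, one standard error of the difference in T1 means is 0.25 × √(4/165) = 0.0389.
- Directly through the T1 weight: 0.0389 × 2/365 = 0.0002 QALY, which is negligible.
- Through persistence, with slope b of mean utility over follow-up on T1 utility: 0.0389 × b × 91/365. For b = 0.3 this is 0.0029; for b = 0.5 it is 0.0049.

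**6. Death rule.** For a patient with utility 0.7 who dies at day 30, ending the area at death gives 0.7 × 30/365 = 0.058 QALY, the same as setting utility to 0 afterwards. Imputing 0.7 to day 91 would give 0.7 × 91/365 = 0.175. The two differ only if values after death are treated as missing and filled in.

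**The case against.** **Nothing in the schedule is contradictory.** The one-month measurements exist (cost diary and discrete choice experiment), and three EQ-5D readings is a choice, not an error. That stands: the T3 point is an improvement to a design choice.

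**A fourth reading can make one patient's QALY worse.** Take utilities 0.5, 0.6, 0.4 and 0.7 at T1 to T4. The area is 0.134 QALY with T3 and 0.161 without, a gap of 0.027. If the dip of 0.23 below the line lasted only 10.5 days (the Dutch average stay quoted in the Discussion, used here as an assumption), the true loss is 0.23 × 10.5/365 = 0.007. The three-point curve is then off by 0.007 and the four-point curve by about 0.021. This is right for that patient, but it does not settle the arm comparison. A form at a fixed date catches some patients in a dip and misses others, and the arm average estimates mean utility at that date. For the same reason the 0.027 must not be read as a bias between arms.

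**Adjustment may already be intended.** A reader might infer that T1 utility is not adjusted for. The text does not support so firm a claim: the general rule covers all secondary outcomes, and a ratio of mean differences is compatible with adjusted means. What remains is that the economic sections are silent and no covariates are named for QALYs.

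**The death sentence is general and was not written for QALYs.** A reader might infer that patients who die will be credited with later utility. The text does not say so, and stopping the area at death gives the right answer. Only an ambiguity remains, of a kind that an analysis plan could settle.

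**Readmissions are analysed in their own right**, and QALYs are one of several economic outcomes. That stands and limits the consequence.

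**Conclusion.** The point holds in a limited form. The EQ-5D schedule puts about 96% of follow-up time on one straight line although a suitable visit exists at one month, and the QALY difference has no stated adjustment for a baseline that is already collected. Both are inexpensive to improve.

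The expected effect on the arm difference is modest: about 0.003 to 0.005 QALY for a one-standard-error T1 imbalance, resting on an assumed utility SD of 0.25 and slopes of 0.3 to 0.5. The gain from T3 cannot be sized from the document; it depends on how far the arms depart from the line at one month.

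A reader might also infer that most recovery falls after day 7. The document does not show this. Its only recovery figure is a fall in CCQ from 3.8 to 2.6 between admission and the end of supervised treatment in the pilot. Nor does the QALY argument give a reason to add the CCQ at T3.

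**What to change.** 1. **Table 2:** add the EQ-5D at T3 for patients not yet past that visit. The cost is one short form at an existing visit. Patients already past T3 keep three points, so report a sensitivity analysis that uses three points for everyone. The number who could still gain a reading is not given; 85 of a planned 165 had been treated when the sample size was recalculated. Randomisation in blocks of 6 per location should leave patients before and after the change roughly balanced between arms.
2. **Economic evaluation and Cost-effectiveness:** within each bootstrap replicate, estimate the QALY difference by regression on treatment, T1 EQ-5D and centre, and use that estimate in the ratio, the planes and the acceptability curves. This brings these sections into line with the analysis of covariance promised under Data analysis. It needs no new data.
3. **Data analysis (clarification only):** state that, for QALYs and costs, utility and costs are zero from the date of death, and that imputation or weighting applies only to living patients with missing forms. The cost is one sentence.

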### Randomisation procedure

On the third day of admission clinical stability is assessed in order to determine whether patients can be randomised. This design for randomisation is adapted from the Spanish study performed by Diaz et al. [21] although the criteria for clinical stability were adapted to represent the current practice in the participating hospitals and because of the difference in treatment package patients receive at home. Patients need to meet the following criteria to be randomised: 1 acceptable general health defined as decrease of physical complaints, non dependency of therapies that can not be given at home and being able to visit the toilet independently; 2 normal or moderately increased blood sugar levels, defined as ≤ 15 mmol/L or ≥ 15 mmol/L while the patient is capable to regulate blood sugars independently at home; and respiratory complaints of dyspnoea, wheezing and rhonchi must have decreased in comparison with day one of admission. A special symptoms scoring list adapted from the one used by Ojoo et al [24] is used for this (see additional file 1: appendix 1). This scoring chart scores the major exacerbation symptoms such as dyspnoea, coughing, mucus production and colour and oedema. By scoring these symptoms daily, improvement or deterioration in comparison with the previous days becomes more visual and supports the pulmonologist when applying the randomisation criteria to the patient.

Randomisation is performed on a 1:1 scale using a computer-generated randomisation list that is placed in sealed envelopes containing the allocation sequence of the two treatment groups. Randomisation is performed per participating location of the hospitals. We chose this procedure to ensure all participating hospitals have a similar proportion of patients in the intervention group and patients in the control group and that the burden for each participating home care organisations is similar. Furthermore, a block size of 6 is applied to create equal numbers in both groups.

The treatment protocol for the following four days is started after randomisation and for the intervention group the process of discharge planning is started.

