#### Primary outcome measure

The changes on the primary outcome measurement, the CCQ, will be analysed with the repeated measurements ANOVA technique. The dependent variable is the change in CCQ score from baseline (T1) to the end of the supervised treatment (T2). Treatment group is considered as independent variable and baseline CCQ score (T1) and centre of treatment are considered as covariates. Age, gender and severity of the disease will also be included in the model as covariates. If necessary, other covariates will be included in the model.

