#### Secondary outcomes measurements

All time-to-event outcomes (i.e. time to readmission and time to death) will be analysed using Kaplan-Meier curves and Cox Proportional Hazards regression model. Event rates (i.e. treatment failures, readmission rates and mortality rates) will be analysed using an appropriate model for count data (e.g. poisson regression or binomial regression)

Differences in outcomes defined as the mean change from baseline (e.g. long-term effectiveness, primary informal caregiver burden, patient- and primary informal caregiver satisfaction and quality of life) will be analysed using repeated measurements ANOVA.

Patient- and caregiver preference for place of treatment will be analysed using a logistic regression model.

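### The economic bootstrap omits the hospital location on which randomisation was blocked, so its intervals will be somewhat too wide if costs or outcomes differ between locations

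*Protocol article*

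**What the plan says.** All references are to the protocol article.

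- **Randomisation procedure.** "Randomisation is performed on a 1:1 scale", "Randomisation is performed per participating location of the hospitals", and "a block size of 6 is applied to create equal numbers in both groups". The stated aim is similar arm proportions in every hospital and a similar burden on each home care organisation.
- **Data analysis (general rule).** "All primary and secondary outcome measurements will be analysed using analysis of covariance". Multilevel analyses for dependency between patients of the same hospital are to be done in addition.
- **Primary outcome measure (under Data analysis).** For the CCQ change from T1 to T2, "baseline CCQ score (T1) and centre of treatment are considered as covariates".
- **Economic evaluation.** The CCQ change from randomisation to day 7 is also a principal health outcome here. The incremental ratio is built from the difference in mean costs between the arms.
- **Cost-effectiveness.** "Uncertainty around the estimates of costs and health outcomes will be addressed by bootstrapping the data". The replicates supply the 95% intervals for the differences in mean costs and effects, the planes and the acceptability curves. No location or centre term and no resampling strata are named.
- **Secondary outcomes measurements (under Data analysis).** Time to readmission and time to death "will be analysed using Kaplan-Meier curves and Cox Proportional Hazards regression model". Event rates get a suitable count model, with the choice left open. Centre is not repeated.

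**The concern.** Blocking within location makes the arms nearly equal in size at every location, so differences between locations largely cancel from the arm contrast. An analysis without location still counts those differences as noise. The estimate is unbiased, but its stated uncertainty is larger than the design warrants.

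Two things are at stake. First, cost-effectiveness is half of the primary research question, and its intervals and acceptability curves would be less sharp than the randomisation allows. Second, the plan treats one quantity in two ways: the day-7 CCQ change is centre-adjusted in the primary analysis and, as written, a plain mean difference in the economic analysis. The general multilevel rule does not settle this, because it is additional and is not tied to the bootstrap. The article also uses three terms (location, hospital, centre) without saying whether they are the same unit.

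**Working it through.** **1. Inputs.** From the article: 1:1 allocation, blocks of 6 per location, α = 0.05, N = 165, and SDs of CCQ change of 0.988 and 0.922. Assumed, because the article gives neither: 3 to 8 locations and an ICC of 0 to 0.20.

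**2. The plan's own figures.** The article states no width for any economic interval, so the sample sizes are the only figures to reproduce.
- t-test: d = 0.4/1.04 = 0.385 gives 107 per arm, total 214, as stated.
- ANCOVA: pooled SD = √[(0.988² + 0.922²)/2] = 0.956, and f = (0.4/0.956)/2 ÷ √(1 − 0.288²) = 0.2186. The rounded f = 0.22 gives 165, as stated; the unrounded value gives 167.

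**3. Expected size by algebra.** With K locations of equal size and intraclass correlation ρ, the expected share of variance lying between the locations is about s = ρ(K−1)/K ÷ [ρ(K−1)/K + 1 − ρ]. Near-equal arms within location remove this share from the contrast, so the ratio of the standard error without location to that with location is about 1/√(1 − s).

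| ICC | K = 3 | K = 5 | K = 8 |
|---|---|---|---|
| 0.05 | 1.017 | 1.021 | 1.023 |
| 0.10 | 1.036 | 1.043 | 1.047 |
| 0.20 | 1.080 | 1.095 | 1.104 |

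Example for K = 5, ρ = 0.20: s = 0.16/0.96 = 0.167, and 1/√0.833 = 1.095.

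**4. Simulation of the design.** Location-stratified blocks of 6, N = 165, 3, 5 or 8 locations, 2000 runs. The bootstrap standard error of a mean difference without strata was divided by the one stratified by arm and location. The ratio was about 0.99 at ICC 0, 1.00 at 0.02, 1.01-1.02 at 0.05, 1.03-1.04 at 0.10 and 1.07-1.10 at 0.20. It falls slightly below the algebra because using location costs degrees of freedom. Coverage of the unstratified interval was 94.4-96.8%.

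**5. On the CCQ scale.** Half-width without location: 1.96 × 0.956 × √(4/165) = 0.29 points. Using location would trim 0.003-0.005 points at ICC 0.05 and 0.02-0.03 at ICC 0.20.

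**6. Simulation of the regression version.** Five locations, N = 165, gamma-skewed costs, 2000 trials with 400 replicates each; location was a covariate in every replicate. The first column is the share of cost variance between locations.

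| Location share | Width, adjusted/unadjusted | Coverage unadjusted | Coverage adjusted |
|---|---|---|---|
| 0.05 | 0.975 | 94.9% | 94.0% |
| 0.10 | 0.951 | 95.8% | 94.7% |
| 0.20 | 0.895 | 96.2% | 94.0% |

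The Monte Carlo standard error is √(0.95 × 0.05/2000) = 0.5 percentage points, so 94.0% is about two standard errors below nominal.

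**7. Readmission and death.** Five locations, 300 runs per setting. The standard error without location divided by that with location was 0.99-1.00 for Cox and 0.87-0.99 for logistic models, so adding location does not narrow these intervals. The estimate moves away from no difference when locations differ strongly: at a true hazard ratio of 1.5 and a location SD of 0.6, the log hazard ratio was 0.39 unadjusted and 0.42 stratified.

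**The case against.** **The article condenses a fuller plan.** It never says that the bootstrap is unstratified, and a difference in mean costs could be an adjusted one. Resampling detail is commonly left to the analysis plan. This stands as far as strata and code go. It does not remove the mismatch between two analyses that the article does describe: centre is named for the day-7 CCQ change in one place and absent in the other.

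**The general rule covers it.** Cost-effectiveness is called the main secondary outcome, so the multilevel rule nominally reaches it. But that rule is additional, speaks of hospital rather than location, and is not connected to the bootstrap, planes or curves.

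**Location variation may be small.** The supervised phase is planned as seven days in both arms, which limits variation in the initial stay. Later costs can still vary. If locations do not differ, nothing is gained.

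**Stronger readings that a reader might infer.**
- *That the intervals are wider as a matter of fact.* This depends on a between-location variance that the article does not give.
- *That coverage climbs well above 95%.* For a location share of 0.20, theory gives 1.96 × 1.118 = 2.19 standard errors, or 97.2%. The simulation with skewed costs gave 96.2%, and 94.9% at a share of 0.05.
- *That the readmission and death intervals are too wide as well.* Adding location does not shorten them, the general rule already provides for hospital dependency in those outcomes, and the count model is left open.

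**Conclusion.** The point holds for the economic evaluation only, and conditionally. The design uses location and the primary model uses centre, but the bootstrapped cost and effect differences are described without either. If costs or outcomes differ between locations, the economic intervals will be conservative. With 3 to 8 locations and N = 165, the excess in standard error is 1-2% at ICC 0.05, 3-4% at 0.10, 7-10% at 0.20 and nil at 0. At the top of that range this is like discarding information worth 14-21% more patients (1.07² = 1.14, 1.10² = 1.21); at ICC 0.05 it is 2-4%. The number of locations and the ICC are assumptions. Nothing here is invalid, and the point is a minor improvement. For readmission and death, only a clarification is needed.

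**What to change.** - **Cost-effectiveness:** resample within arm. In each replicate, estimate the cost and effect differences from a regression on treatment with randomisation location as a covariate. Use these differences for the intervals, planes and acceptability curves.
- **Primary outcome measure:** define centre as the randomisation location.
- **Secondary outcomes measurements:** state that the hospital adjustment in the general rule applies to the readmission, mortality and treatment-failure models.

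The cost is a few lines of wording and code. Location is already known from randomisation, and no new data or patients are needed. The statistical price is a few degrees of freedom (4 with five locations) and possibly slight undercoverage with skewed costs, about 94% in the simulation.
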